## Abstract

**Background:**

Malnutrition is highly prevalent in hospitalized patients and results in a worsened clinical course as well as an increased length of stay, mortality, and costs. Therefore, simple nutrition screening systems, such as CIPA (control of food intake, protein, anthropometry), may be implemented to facilitate the patient’s recovery process. The aim of this study is to evaluate the effectiveness and cost-effectiveness of implementing such screening tool in a tertiary hospital, consistent with the lack of similar, published studies on any hospital nutrition screening system.

**Methods:**

The present study is carried out as an open, controlled, randomized study on patients that were admitted to the Internal Medicine and the General and Digestive Surgery ward; the patients were randomized to either a control or an intervention group (*n* = 824, thereof 412 patients in each of the two study arms). The control group underwent usual inpatient clinical care, while the intervention group was evaluated with the CIPA screening tool for early detection of malnutrition and treated accordingly.

CIPA nutrition screening was performed upon hospital admission and classified positive when at least one of the following parameters was met: 72 h food intake control < 50%, serum albumin < 3 g/dL, body mass index < 18.5 kg/m^2^ (or mid-upper arm circumference ≤ 22.5 cm). In this case, the doctor decided on whether or not providing nutrition support.

The following variables will be evaluated: hospital length of stay (primary endpoint), mortality, 3-month readmission, and in-hospital complications. Likewise, the quality of life questionnaires EQ-5D-5 L are being collected for all patients at hospital admission, discharge, and 3 months post-discharge. Analysis of cost-effectiveness will be performed by measuring effectiveness in terms of quality-adjusted life years (QALYs). The cost per patient will be established by identifying health care resource utilization; cost-effectiveness will be determined through the incremental cost-effectiveness ratio (ICER). We will calculate the incremental cost per QALY gained with respect to the intervention.

**Discussion:**

This ongoing trial aims to evaluate the cost-effectiveness of implementing the malnutrition screening tool CIPA in a tertiary hospital.

**Trial registration:**

Clinical Trial.gov (NCT02721706).

First receivevd: March 1, 2016

Last updated: April 8, 2017

Last verified: April 2017

## Background

Hospital malnutrition (HM) is a frequent condition in developed countries; its prevalence ranges from 25 to 50%, depending on the study population and the detection method [1–4]. This type of malnutrition is associated with the patient’s underlying condition, so that it may be triggered either by the disease-related symptoms (dysphagia, vomiting, diarrhea, malabsorption, etc.), thereby reducing food intake or increasing losses, or by an associated, increased caloric and protein requirement that the patient cannot cover.

Malnutrition in hospitalized patients leads to an exacerbated clinical course, with additionally emerging comorbidities and worsened functional capacity, which in turn lead to a longer hospital stay, increased mortality and health care costs [3–5]. It is, therefore, essential to detect these patients using nutrition screening techniques at hospital admission and thus try to improve their prognosis through nutrition therapy.

HM is as frequent as underrated, so that only few European countries and hospitals apply nutrition screening on admission. In the Spanish multicenter study PREDYCES, where screening was performed using Nutritional Risk Screening 2002 (NRS 2002), 23% of the hospitalized patients were found to be malnourished [6]. In addition, that malnourished subgroup underwent an aggravated clinical course during their hospital stay [2]. Based on these results, nutrition screening pilot projects are now being implemented in different hospitals throughout the country.

There is no gold standard for hospital nutrition screening, despite the high number of existing screening tools. It is, therefore, best to incorporate one that can be applied according to the hospital characteristics and that primarily identifies patients with the poorest clinical prognosis. In the University Hospital *Nuestra Señora de Candelaria* (HUNSC), Santa Cruz de Tenerife, Spain, the nutrition screening method CIPA (control of intakes, proteins, anthropometry) was designed by employing tools commonly used in clinical practice.

When CIPA screening was compared with Subjective Global Assessment (SGA) [7, 8] — the standard method for validation, nonetheless not a gold standard — in patients with a non-surgical pathology, those who resulted positive by CIPA screening had a longer mean stay than patients with a negative result (19.53 vs 12.63 days; *p* <0.001); this data was not detected by SGA screening. On the other hand, patients identified as positive by either method comprised more cases of death both in hospital (7.6% vs 1.4%, *p* = 0.026; CIPA screening) as well as by the first month post-discharge (12.7% vs 3.5%, *p* = 0.012) [9]. Therefore, in this group of patients, the CIPA screening tool detected those with a comparably worsened clinical course more efficiently than the SGA method.

Although malnourished patients have a worse prognosis and generate higher costs than the rest, the cost-effectiveness of performing a hospital nutrition screening is not sufficiently studied. Only few studies have performed an economic evaluation of a malnutrition screening in hospitalized patients. Kruzienga HM et al. analyzed the implementation of the screening method SNAQ (Short Nutritional Assessment Questionnaire) and concluded that its implementation was cost effective, mainly in the fragile patient [10]. The NICE guidelines on Nutrition Support in Adults [11] indicated that screening is likely to be cost effective but highlighted a high degree of uncertainty due to “the weakness in the methodologies and designs of identified studies.”

This study aims to shed light onto this area and study the clinical and economic impact through a randomized, controlled trial on the implementation of a nutrition screening method, in this particular case the CIPA method, in a tertiary hospital.

## Methods

### Trial design

This study is a two-armed, randomized, controlled trial, comprising an intervention arm, where patients were screened for malnutrition using CIPA at hospitalization, and a control arm, where patients were not screened but diagnosed according to standard clinical practice.

### Subjects

Patient inclusion criteria:Patient admitted to the hospitalization ward of Internal Medicine or General and Digestive Surgery of the HUNSC.Formal consent to participate in the study.Age of 18 or more years.

Patient exclusion criteria:Patient treated with nutrition support before finishing the CIPA screening procedure.Patient transferred from other ward.Patient with an expected length of stay of less than 72 h.Unfeasible CIPA screening for whatever reason.Patient with poor short-term prognosis.Bed assignment at hospital admission non-randomized.Patient participating in other research study.Pregnancy.

### Setting and recruitment

Patients were recruited in the hospitalization area of the HUNSC, in the wards of Internal Medicine and General and Digestive Surgery. These departments were chosen for integrating the patients with the highest clinical variability and comorbidity. Recruitment was conducted in two phases: the first, at the time of hospitalization, in which the patient was confirmed to meet the inclusion or exclusion criteria and asked to sign the informed consent, thereby becoming potentially eligible. The second phase took place at 72 h, when the result of the CIPA nutrition screening was obtained, point at which the patient was verified not to have received nutrition treatment by that time and eventually became part of the sample. Otherwise, the patient was excluded from the study according to criterion 1).

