### Random assignment

Both scheduled and emergency admission patients were allocated by the department of hospital admission to one of the participating wards, following the randomization plan, which was generated by simple random sampling and delivered by the data manager of the project. This randomization facilitated trial execution and prevented protocol errors, as the group to which each patient belonged was defined by its location.

Both the Internal Medicine and the General and Digestive Surgery ward are divided into two hospitalization wings. At the time of the study, due to the progressive introduction of the nutrition screening in the HUNSC, one of the two wings of either ward conducted the CIPA screening at hospital admission (intervention wards), while the other did not (control wards, where standard practice was performed).

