#### Statistical analysis

Descriptive data analysis will present qualitative variables as frequencies and percentages, and continuous variables as means, medians, and standard deviations. Normality shall be verified by the Kolmogorov-Smirnov normality test. In bivariate analysis, depending on the nature of the variables, the parametric hypothesis test Student’s *t*-test or the non-parametric Mann-Whitney test will be used. To assess the effects of the intervention, changes in the primary and secondary outcomes will be analyzed by a between-group ANCOVA variance test. The analysis will control for the type, age, and sex of the patient, as well as the responsible medical unit. Patients admitted to Internal Medicine will be categorized into the four groups (1) cardiovascular, (2) neoplastic, (3) infectious, and (4) other patients, whereas patients in the Digestive and General Surgery services will be divided into the categories (1) neoplastic, (2) infectious, (3) obstructive, (4) inflammatory, and (5) others. The economic evaluation and statistical analyses of individual variables will be conducted in accordance with the intention-to-treat principle.

All tests will be two-sided with a type I error of 5%. Statistical analyses will be performed using the Statistical Package for Social Sciences (SPSS v.23, Chicago, IL, USA).

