It is worth noting that the SNHS only covers the cost of post-discharge nutrition supplements under very specific conditions, e.g., in cancer patients, patients with dysphagia, neurodegenerative diseases, and similar. Consequently, many of the patients who need nutrition support in hospital would not be able to continue after their discharge. For this reason, the number of patients with continued nutrition supplementation after discharge is expected to be rather low in this study.

At the same time, due to training and greater awareness about diagnosis and treatment of malnutrition among the clinical staff of the HUNSC, particularly in the surgical wards, the number of patients excluded for having nutritional support before finalizing the CIPA screening has been higher than expected, which led to an extension of the recruitment period.

Therefore, with the scientific rationale in favor of a nutrition management of malnourished patients and with tools for early detection of this condition at hand, it is foreseeable that the implementation of a cheap and simple hospital nutrition screening results in a cost-effective intervention. However, properly designed and methodologically unbiased studies are required to evaluate this relationship. Given the scarcity of literature in regard to this type of evaluations, we hope to fill the evidence gap between hospital nutrition screening and health care cost savings with this study, and, if proven cost effective, promote the universal implementation of the CIPA screening system in hospitals through appropriate political strategies.

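### Allocated, consented patients are excluded at 72 h for early nutrition support, so the planned comparison is not the intention-to-treat analysis that the protocol promises

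*Protocol article*

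**What the plan says.** All references are to the protocol article.

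- **Allocation.** Under Random assignment, the admissions department places patients in a wing according to the randomization plan, and "the group to which each patient belonged was defined by its location". One wing of each department runs CIPA and the other does not.
- **Two-step recruitment.** Under Setting and recruitment, criteria are checked and consent is sought at admission, which makes the patient only potentially eligible. The second step comes with the CIPA result, three days later: "the patient was verified not to have received nutrition treatment by that time and eventually became part of the sample". Anyone who fails this check leaves the study under the first exclusion criterion.
- **Exclusion criteria.** Under Subjects, the first criterion is "Patient treated with nutrition support before finishing the CIPA screening procedure". A separate one is "Unfeasible CIPA screening for whatever reason".
- **Blinding.** Patients and the clinical research team know the group.
- **Analysis.** Under Statistical analysis, the economic evaluation and the analyses of individual variables "will be conducted in accordance with the intention-to-treat principle".
- **What happened.** The Discussion reports that "the number of patients excluded for having nutritional support before finalizing the CIPA screening has been higher than expected". It attributes this to training and greater awareness among clinical staff, particularly on the surgical wards, and says that recruitment had to be extended. It gives no count and no split by arm.

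**The concern.** Intention to treat means that patients are analysed in the arm to which they were allocated, whatever happens afterwards. Here, membership of the sample depends on what happens in the first 72 hours on the allocated wing, when the intervention is already under way on one side. Randomization protects the comparison of everyone allocated. It does not protect the comparison of those who remain after a filter that the arm itself may influence.

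If early support removes more patients from one arm, or a different kind of patient, mean length of stay can differ between the arms with no effect of screening. Even if removal is balanced, the result describes only patients not given nutrition support in the first three days. That is a narrower group than the one to which the Discussion hopes to extend the tool.

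**Working it through.** **1. The passages side by side**

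| Step | When | Source |
|---|---|---|
| Wing, and so arm, assigned | Admission | Random assignment |
| Criteria checked, consent sought | Admission | Setting and recruitment |
| BMI or arm circumference taken | Ward entry | Anthropometric determinations |
| Albumin requested automatically | Within 48 h | Biochemical determinations |
| Food-intake result; check for prior nutrition treatment | 72 h | Setting and recruitment; Interventions |
| Treated patients excluded | 72 h | Setting and recruitment; Subjects, first criterion |

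Exclusion follows allocation and consent, and no section keeps the excluded patients in any analysis set. The conflict with the intention-to-treat statement follows from the text alone.

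**2. Could exclusion depend on arm?** Under Interventions, any one of the three components makes the screen positive. In the CIPA wing, a low BMI or low albumin can therefore be known before 72 h, and support started on it would meet the first exclusion criterion. In the control wing, early support arises from the doctor's routine judgement, and that doctor may also request nutrition parameters. Arm dependence is therefore possible, but it is not documented.

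**3. The plan's own sample size.** Inputs from Sample size calculation: difference 2.6 days, SDs 8 and 13.3, 90% power, two-sided 5%, 10% losses.
- Averaged SD = √((8² + 13.3²)/2) = 10.975.
- n per arm = 2 × (10.975 × (1.960 + 1.282)/2.6)² = 374.4.
- 374.4 × 1.1 = 411.9, so the stated 412 reproduces.

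The sample size is not in dispute. The 10% allowance replaces numbers; it cannot correct selection.

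**4. Illustration of size**

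Inputs: mean stays of 19.53 days (CIPA-positive) and 12.63 days (CIPA-negative), from the Background, in non-surgical patients; 221 patients in total, from the Discussion. The positive/negative split is not printed. Reading both pairs of mortality percentages in the Background as CIPA-positive versus CIPA-negative, 79/142 is the only split of 221 that gives all four: 6/79 = 7.6%, 2/142 = 1.4%, 10/79 = 12.7%, 5/142 = 3.5%.

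- Overall mean μ = (79 × 19.53 + 142 × 12.63)/221 = 15.10 days.
- If an excess share x of one arm is removed, with mean stay L, that arm's mean falls by μ − (μ − xL)/(1 − x) = x(L − μ)/(1 − x).
- With L = 19.53, L − μ = 4.43.

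| Excess removed x (assumed) | Shift in days | Share of 2.6 days |
|---|---|---|
| 5% | 0.05 × 4.43/0.95 = 0.23 | 9% |
| 10% | 0.10 × 4.43/0.90 = 0.49 | 19% |
| 15% | 0.15 × 4.43/0.85 = 0.78 | 30% |
| Equal removal of comparable patients | 0 | 0% |

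Positives are 79/221 = 36%, so a 15% excess means that about 0.15/0.357 = 42% of one arm's positives are removed over and above the other arm. That is a demanding assumption.

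**5. Effect on the test.** With 412 × 0.9 ≈ 371 analysed per arm, the standard error is 10.975 × √(2/371) = 0.806 days. Under a normal approximation, a spurious difference of 0.5 day raises the two-sided 5% error to about 9.5%.

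**The case against.** The strongest reply is that the document shows no difference in exclusion between the arms. The Discussion gives a cause for the excess exclusions, staff training and awareness, and that cause is not tied to an arm. Control doctors can start early support as well. The treatment pathway under Interventions begins after a positive result, and the result is placed at 72 h; nothing says that support was started on a partial result. If comparable patients are removed equally, the comparison is unbiased. All of this stands, and it limits what can be said about bias. It does not answer the conflict with the intention-to-treat statement, which holds whatever the split.

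Two stronger readings are tempting but not supported:

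- **That infeasible screening removes patients at 72 h only in the CIPA arm.** The 72-h removal is tied to the first exclusion criterion alone. Feasibility may have been judged in both wings at admission, when the criteria were checked. The article does not say how the criterion was applied where no screening takes place. That is a question of symmetry, not evidence of one-sided loss.
- **That those removed have the longest stays, so the bias is a large part of the target.** The 19.53-day figure describes CIPA-positive non-surgical patients, not patients given early support, and the Discussion locates the excess particularly in surgery. A longer stay for those removed would enlarge the shift, but the document offers no value for it.

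It is also fair to say that the remedy depends on consent terms. Patients removed at 72 h were only potentially eligible, and whether their records may be used is not stated.

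**Conclusion.** The point holds as a contradiction within the protocol article: a stated exclusion acts after allocation, and the stated analysis principle does not allow it. Confidence in this is high and needs no assumption.

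That the exclusion differs by arm is a reasonable inference from the timing of the CIPA components, and no more. The size and direction of bias cannot be determined from the document. The 0.2 to 0.8 days is an illustration. It rests on an assumed excess removal of 5% to 15% of one arm, on non-surgical stays, on a back-derived 79/142 split, and on those removed staying as long as CIPA-positive patients. If the CIPA wing lost more such patients, its mean stay would look shorter; if the control wing did, the reverse. Because the primary endpoint is exposed and the article describes analysis as still to come, this should be settled before the data are analysed.

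**What to change.** 1. Define the primary analysis set as all patients allocated to a wing who consented at admission, analysed by assigned wing, whatever happened by 72 h. Take length of stay, mortality and readmission for those removed from the electronic record, where their consent permits.
2. Keep the 72-h sample as a secondary set, labelled as such.
3. Report exclusions at 72 h by arm, reason and department.
4. State when and how feasibility of CIPA was judged in the control wing, and apply that criterion in the same way in both arms.
5. If the records of removed patients cannot be used, drop the intention-to-treat label and state the limitation.

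**Cost.** A change of wording, a check of the consent terms, and a record extraction of unknown size, since the number removed is not reported. The effect estimate may be somewhat diluted, and later EQ-5D scores will be missing for the removed patients, which affects the QALY analysis more than the primary endpoint. The planned 412 per arm need not change.

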### Random assignment

Both scheduled and emergency admission patients were allocated by the department of hospital admission to one of the participating wards, following the randomization plan, which was generated by simple random sampling and delivered by the data manager of the project. This randomization facilitated trial execution and prevented protocol errors, as the group to which each patient belonged was defined by its location.

Both the Internal Medicine and the General and Digestive Surgery ward are divided into two hospitalization wings. At the time of the study, due to the progressive introduction of the nutrition screening in the HUNSC, one of the two wings of either ward conducted the CIPA screening at hospital admission (intervention wards), while the other did not (control wards, where standard practice was performed).

### Blinding

Due to the nature of the intervention, neither enrolled patients nor the clinical research team could have been blinded to the group they belonged to, although patients were not informed until they signed the consent of their group. The doctors responsible for treatment did not know whether or not patients were enrolled in the study for not to create an intervention bias on the patient. Data analysis is going to be blinded to the intervention assignment.

### Interventions

Patients in the intervention group were subjected to CIPA nutrition screening, which resulted positive if one of the following conditions was met: (1) 72 h food intake control below 50% [12]; (2) serum albumin < 3 g/dL; (3) body mass index (BMI) < 18.5 kg/m^2^ or mid-upper arm circumference (MUAC) ≤ 22.5 cm [13], the latter when the patient could not be weighed and measured. The flow chart in Fig. 1 reflects the health care personnel’s staff’s tasks to accomplish the screening process.

**Fig. 1 Fig1:**
[figure not shown]
Health care staff’s tasks to accomplish CIPA screening

When patients were admitted through the emergency room or on a scheduled basis for any medical reason, the nutrition screening process started on ward admission. Conversely, if patients were admitted for scheduled surgery, nutrition screening began thereafter, when they arrived at the ward.

In case of a positive screening result, the attending doctor would evaluate the adequacy of a nutrition treatment. To this end, if the patient was unable to feed orally, the doctor requested a referral to the Endocrinology and Nutrition Service, whose doctors and nurses were in charge of a nutrition assessment and the administration of the artificial nutrition they considered appropriate. In the case the patient was able to eat by mouth, a dietitian would adjust the diet and monitor the patient’s progress on the third and tenth day, if necessary. In addition, according to the internal protocol, the patient received two specific oral nutrition supplements (ONS) per day, depending on their comorbidities.

As for the control group, routine clinical practice without any nutrition screening was carried out, so that the responsible doctor may have requested the nutrition parameters and considered specific nutrition treatment if appropriate.

Regardless of the group they belong to, patients with nutrition support during hospitalization may have continued that prescribed support for at least three more months past discharge, provided that the responsible doctor considered the measure appropriate and their pathology was included in the financing list of such treatments of the Spanish National Health System (SNHS). Figure 2 shows the intervention algorithm.

